### Data Analyses

First, demographics and behavioral baseline assessment of experimental and control groups will be compared, to test any potential difference between groups for variables relevant to the aim of the study, together with the variables related to the asymmetry scores as described in section “Procedure”. Thereafter, a series of GLMs is intended to be carried out to compare the effect of the active NF training with those of the sham NF training. For doing that, a mixed factorial ANOVA 2 × 2, considering Phase (pre vs. post) and Condition (experimental vs. sham) as the independent variables will be carried out for each dependent measure (i.e., separate left and right β and θ frequencies power during the linguistic tasks; left β/θ and right β/θ EEG power in resting state and during the linguistic tasks; accuracy and reaction times during the linguistic tasks, reading task, and RAN; accuracy in the digit span task). A correction for multiple comparisons will be applied (i.e., the Bonferroni correction). A sample size of 40 was calculated to be enough to achieve a statistical power of 0.87, for medium effect size (η^2^ = 0.06), by setting alpha at 0.05, in the GLMs we planned to carry out to test the effectiveness of the NF intervention.

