### Participants

Forty participants will be enrolled in the study. Eligibility of participants will be checked based on the following inclusion criteria: (a) adults aged 18–35 years; (b) to have a diagnosis of DD (ICD-10 code: F81.0) (World Health Organization, 1992) or a reading performance of at least 1.5 SD below the norm. Exclusion criteria include intellectual disability, psychiatric conditions, comorbidity with neurodevelopmental disorders (e.g., ADHD), neurological disorders, epilepsy, and enrollment in linguistic or literature university courses. Participants will be recruited by advertising the study through the Learning Disability services of two university campuses. Potential participants will have to provide demographic, clinical (i.e., psychiatric and neurological conditions), and educational information (i.e., years of education, field of study, average grades) and to complete a few self-report standardized questionnaires about their reading abilities. Potential participants who received a diagnosis of DD made by an independent clinician prior the enrollment in the investigation will be asked to share their clinical documentation with the researchers.

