### Procedure

Participants who will respond to the recruitment advertisement will receive a detailed description of the experimental procedure and written informed consent to participate in the study *via* email. If they will provide their consent, participants will be asked to complete an online screening phase to check their eligibility. Eligible participants will be selected based on the inclusion and exclusion criteria of the study and will be randomly assigned to one of two experimental conditions (i.e., active NF training; sham NF training; and 1:1 ratio).

The study will include two experimental sessions: A preliminary screening session will be conducted to record EEG data of participants during resting state (i.e., eyes open 3-min) and two linguistic tasks (see section “Neurophysiological Measures”). This phase will provide information about EEG band variability. Data of participants who will have shown an abnormally low α frequency (i.e., α peak frequency below about 8.5 Hz at TP during resting-state), which could potentially make calculations on the β/θ ratio misleading, will be excluded from the analyses. EEG data collected during the screening phase will be elaborated; A measure of hemispheric asymmetry will be calculated (i.e., TP7–TP8) to (1) monitor whether and to what extent the degree of asymmetry in the ratio can influence the outcomes of the following training, and (2) to allocate participants equally to the experimental and the placebo conditions. Indeed, participants will be assigned to one of two experimental conditions (i.e., active NF training; sham NF training; and 1:1 ratio) using stratified randomization based on the β/θ asymmetry scores.

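### The 2 × 2 mixed ANOVA amounts to a change-score test: valid under randomisation, but less efficient than ANCOVA and without a term for the asymmetry score used to stratify

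*Protocol article*

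**What the plan says.** The Data Analyses section fixes one model for every dependent measure: "a mixed factorial ANOVA 2 × 2, considering Phase (pre vs. post) and Condition (experimental vs. sham) as the independent variables". No covariate is named. The Expected Results section identifies the Phase × Condition interaction as the effect of interest.

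The Procedure section says that participants are allocated "using stratified randomization based on the β/θ asymmetry scores", where the score is the left minus right β/θ ratio recorded at screening. In Data Analyses this score appears only among the variables compared between groups at baseline, a comparison made "to test any potential difference between groups for variables relevant to the aim of the study". Elsewhere it has a larger role. The Introduction makes its influence on the training outcome the second purpose of the study, and Expected Results anticipates larger improvements in people with larger scores.

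On size and power: "Forty participants will be enrolled in the study", allocated 1:1. "A sample size of 40 was calculated to be enough to achieve a statistical power of 0.87", for η² = 0.06 and "by setting alpha at 0.05". No pre–post correlation is given.

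**The concern.** Two pieces of information are collected before training and left out of the outcome model: the pre-training value of the same measure, as a covariate, and the stratification score. A change score fixes the coefficient of the baseline at 1. When the true regression slope of post on pre is below 1, this over-corrects. The estimate carries avoidable noise, and in any one trial a chance baseline difference feeds into it through regression to the mean. Significance tests of baseline differences do not repair this. After randomisation they test only chance, and nothing in the section acts on their result.

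At stake is precision in a trial of 40 people. There is also a mismatch between design and analysis: allocation is balanced on a score thought to be prognostic, and the analysis then leaves that score out, which generally makes standard errors conservative.

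**Working it through.** **Inputs.** From the article: N = 40 (20 per arm), η² = 0.06, alpha = 0.05, stated power 0.87. Not in the article: r, the pre–post correlation, which is treated as an assumption throughout.

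**1. The planned test.** With two time points, the interaction F on (1, 38) degrees of freedom is the square of the t statistic comparing mean change between arms.

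**2. Reproducing 0.87.** f² = 0.06/0.94 = 0.0638. For the within–between interaction with two measurements, λ = f² × N × 2/(1 − r).
- r = 0: λ = 5.11, power 0.60
- r = 0.3: λ = 7.29, power 0.75
- r = 0.5: λ = 0.0638 × 80/0.5 = 10.21, power 0.876 (0.869 with the conventional f = 0.25)
- r = 0.7: λ = 17.02, power 0.98

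Only r of about 0.46 to 0.53 comes within two points of 0.87. The stated power is therefore reproduced, with r ≈ 0.5 implied.

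**3. Variance ratio.** With equal pre and post variance σ², the per-person variance is 2(1 − r)σ² for a change score and (1 − r²)σ² after baseline adjustment. The ratio is (1 − r²)/[2(1 − r)] = (1 + r)/2.

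| r | Ratio | Variance saved |
|---|---|---|
| 0.3 | 0.65 | 35% |
| 0.5 | 0.75 | 25% |
| 0.7 | 0.85 | 15% |
| 0.8 | 0.90 | 10% |
| 0.9 | 0.95 | 5% |

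This ratio is a large-sample result. A simulation at 20 per arm, which includes the cost of estimating the slope, gave 0.771 at r = 0.5, a saving of about 23%.

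**4. Power at r = 0.5.** λ rises to 10.21/0.75 = 13.62. Power is 0.949 on 37 error degrees of freedom (baseline covariate only) and 0.948 on 36 (baseline plus asymmetry score, with no further variance reduction credited to the score). With f = 0.25 it is about 0.944. With the simulated ratio, λ = 10.21/0.771 = 13.24 and power is about 0.94. Equivalently, since 40 × 0.75 = 30, about 30 participants analysed by ANCOVA would give the planned 0.87.

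**5. Stratification score.** Its correlation with the outcomes is not given, so any gain beyond step 4 cannot be calculated.

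**6. Screening-session EEG as a second baseline.** If all three correlations are 0.5, the ratio to the change score is 0.667. If screening correlates only 0.3 with post, it is 1 − (0.25 + 0.09 − 0.15)/0.75 = 0.747, almost no better than one baseline. The document cannot settle which applies.

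**The case against.** The planned analysis is standard and defensible. Under randomisation the interaction test is unbiased and holds its type I error. It matches the stated hypothesis, and its stated power can be reproduced. All of this stands, so the point is about efficiency and not validity.

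Two stronger readings are tempting. A reader might infer that the plan ignores baseline and the asymmetry score altogether. It does not: a change score uses the baseline by subtraction, and the asymmetry score is used in allocation and in the baseline comparison. A reader might also infer that a quarter of the variance is certainly being lost. That figure belongs to r ≈ 0.5, which is only inferred from the power statement. Pre and post are taken within one visit of about 90 minutes, so r may well be higher. At r = 0.7 the same formula already gives the planned test power of 0.98, and ANCOVA 0.99. One r is also unlikely to fit EEG power, error counts, reaction times and digit span alike.

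The powers above use alpha 0.05, while a Bonferroni correction is planned, so neither 0.87 nor 0.95 is the power of a corrected test. The advantage remains after correction. As an illustration, if the correction spanned the 14 EEG measures that can be counted in the section (8 single-band powers in the two tasks and 6 ratios) and r = 0.5, power would be about 0.54 for the planned test and 0.71 for ANCOVA.

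Finally, covariate detail is often left to an analysis plan. Here, however, the article states its model explicitly with two factors, so adding covariates would change a stated choice.

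**Conclusion.** The point holds as a loss of efficiency that is cheap to avoid. The stated model is a change-score analysis with neither the baseline covariate nor the stratification score, although both are collected and the score is expected to bear on outcome. At r ≈ 0.5, the value implied by the article's own power, ANCOVA saves about 25% of the variance (about 23% at this sample size) and lifts power at alpha 0.05 from about 0.87 to about 0.95. Over r = 0.3 to 0.9 the saving is 35% to 5%. These figures assume equal pre and post variances and come from adjusting for the outcome's own baseline. The additional value of the asymmetry score, or of the screening-session EEG, cannot be quantified from the document. Nothing here shows the planned test to be biased, or the 0.87 to be wrong for that test at uncorrected alpha.

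**What to change.** For each outcome, replace the 2 × 2 ANOVA with an ANCOVA of the post-training value on Condition, adjusting for the pre-training value of the same measure and for the screening asymmetry score used in stratification. Report the adjusted difference between conditions with its 95% confidence interval. Present baseline characteristics descriptively, without significance tests. For EEG outcomes the screening-session value may be added as an optional further covariate. Entering the asymmetry score as a covariate does not by itself test whether the training effect grows with asymmetry; that would need its own Condition × score term.

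The cost is a change of wording and two error degrees of freedom relative to the change-score test (38 to 36), or three if the optional EEG covariate is used. No new data are needed.

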To the best of our knowledge, despite the significant results obtained in previous NF research, no study has investigated a bilateral NF intervention targeting TP activation. The conjunction effect of the left increased and right decreased TP activation was found to be effective in NIBS interventions for Turkeltaub et al. (2012); Costanzo et al. (2016a, b); Younger et al. (2016).

Our hypothesis is to induce a reading performance improvement using bilateral NF to restore the typical TP hemispheric imbalance in the brain (Shaywitz et al., 1998; Sarkari et al., 2002; Eden et al., 2004; Simos et al., 2007; Rimrodt et al., 2009). As compared to NIBS, NF has fewer exclusion criteria and limitations in its application and could be safely applied in pediatric populations.

The present study protocol was designed to test the effect of a single-session bilateral NF protocol aimed at increasing the β/θ ratio in left TP areas and decreasing the β/θ ratio in the contralateral area on bilateral TP hemispheric imbalance during linguistic tasks in adults with DD. The second purpose of the study is to explore whether and to what extent the degree of asymmetry in the β/θ ratio can influence the outcomes of the training. Finally, the study aims at exploring the effect of the novel NF protocol on the reading and phonological skills of participants.

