### Neurophysiological Measures

EEG cortical activity will be recorded using the ProComp5 Infiniti System paired with the BioGraph Infiniti Software (Thought Technology Ltd.) from two active sites placed in TP7 and TP8, according to the International 10–10 system (Nuwer et al., 1998). Two reference electrodes will be placed on the earlobes and two ground electrodes will be placed on the mastoids. The sampling rate will be set at 256 Hz and impedance will be kept below 5 kΩ. Artifact rejection will be performed using both an amplitude threshold (20 μV) and visual inspection.

During the screening session, a measure of hemispheric asymmetry will be calculated by subtracting the right β/θ power ratio from the left β/θ power ratio at TP (i.e., TP7–TP8).

For the NF session, the separate power of the α frequency (8–12 Hz), the δ frequency (1–3 Hz), along with that of the target frequencies (β: 13–21 Hz; θ: 4–8 Hz) and their ratio (β/θ) will be extracted by the BioGraph Infiniti Software and will be considered for the analyses. Pre and post-training EEG recordings will include three phases: (1) resting-state with eyes open for 3 min; (2) a computerized phonological task, in which participants are required to decide whether a list of bi-syllabic word pairs rhymed or not (Spironelli et al., 2006, 2008); and (3) a computerized semantic task, in which participants are required to decide whether bi-syllabic word pairs from a list were semantically related or not. For a detailed description of the linguistic tasks, see Spironelli et al. (2006, 2008). For phases (2) and (3), both response times and accuracy rates will be recorded.

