## Expected Results

According to our hypothesis, the experimental single-session bilateral TP NF protocol (enhancing left β/θ and reducing right β/θ) would restore the typical reading-related inter-hemispheric imbalance in adults with DD. Accordingly, we expect to find an enhanced left β/θ power ratio and a concurrent reduced right β/θ power ratio during the performance of linguistic tasks after the active NF training. Conversely, we expect the control group (i.e., placebo NF training) to maintain an abnormal activation of TP regions during the linguistic tasks (i.e., reduced left β/θ and enhanced right β/θ) and no modulation of the β/θ power ratio after training. In summary, we expect a significant Phase (pre vs. post) × Condition (active NF vs. placebo NF) interaction effect on the modulation of bilateral TP imbalance. Also, we expect these improvements to be greater for those participants with larger asymmetry scores as assessed in the screening phase.

As for the behavioral measures (i.e., reading, RAN, and verbal WM), despite previous evidence on cognitive enhancement after a single-session NF (e.g., Escolano et al., 2014), we did not formulate a specific hypothesis, but instead, we opted for an exploratory approach, due to the potential limited effect size of a novel single-session NF protocol in DD.

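### The predicted Phase × Condition interaction on bilateral TP imbalance has no matching dependent measure: left and right β/θ ratios are tested only separately

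*Protocol article*

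**What the plan says.** The aim, given at the end of the section Dyslexia and Neurofeedback, is the effect of the training "on bilateral TP hemispheric imbalance during linguistic tasks in adults with DD". Expected Results gives the hypothesis in two forms:

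- By component: "we expect to find an enhanced left β/θ power ratio and a concurrent reduced right β/θ power ratio during the performance of linguistic tasks", after active training.
- In summary: a significant Phase × Condition "interaction effect on the modulation of bilateral TP imbalance".

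The Data Analyses section sets one model, a 2 × 2 mixed ANOVA "considering Phase (pre vs. post) and Condition (experimental vs. sham) as the independent variables will be carried out for each dependent measure". Its EEG measures are "separate left and right β and θ frequencies power during the linguistic tasks" and "left β/θ and right β/θ EEG power in resting state and during the linguistic tasks".

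An imbalance index is defined under Neurophysiological Measures, but for one occasion: "During the screening session, a measure of hemispheric asymmetry will be calculated by subtracting the right β/θ power ratio from the left β/θ power ratio". The Procedure section uses it for stratified randomization and to monitor whether asymmetry influences the outcome. In Data Analyses, asymmetry scores appear only in the baseline comparison of the groups.

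**The concern.** A Phase × Condition interaction on imbalance needs imbalance as the dependent measure, or a Hemisphere factor and the three-way interaction. The plan has neither, so the interaction named in Expected Results does not correspond to any listed test. Imbalance must be inferred from two separate results, and the plan does not say how.

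Two errors are possible. One side may be significant and be read as a changed imbalance, although the two sides were never compared. Or a real change in imbalance may be missed because neither side, or only one, reaches significance alone. The central neurophysiological conclusion of the trial is at stake.

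**Working it through.** **Inputs from the protocol article.** N = 40, allocated 1:1, so 20 per arm; η² = 0.06; α = 0.05; stated power 0.87; Bonferroni correction with the number of tests not given.

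**Assumptions, because the article gives no value.** Pre-post correlation ρ = 0.5; between-hemisphere correlation of change r from 0 to 0.7; equal and opposite effects on the two sides unless stated otherwise. All figures are at α = 0.05 before Bonferroni, except where a family size is named.

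**Step 1: the stated power.** f² = 0.06/0.94 = 0.0638. For the within-between interaction with two phases, λ = f² × N × 2/(1 − ρ) = 0.0638 × 40 × 2/0.5 = 10.21, with 1 and 38 df. Power is 0.876, which reproduces 0.87. It depends on ρ: 0.60 at ρ = 0, 0.75 at 0.3 and 0.98 at 0.7.

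**Step 2: the planned effect in SD of change.** With 20 per arm, λ = d² × 20/2, so d = √(10.21/10) = 1.01.

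**Step 3: the difference score.** For effects +d on the left and −d on the right, left minus right has mean effect 2d and SD √(2(1 − r)). Its standardized effect is 2d/√(2(1 − r)) = d√(2/(1 − r)). The multiplier is 1.41 at r = 0, 2.00 at 0.5 and 2.58 at 0.7.

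**Step 4: power.** Single and difference tests are from the noncentral t with 38 df; joint significance in the predicted directions is from simulation.

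| Effect per side | Each separate test | Both significant | Difference test |
|---|---|---|---|
| 1.01 SD (planned) | 0.88 | about 0.76 | at least 0.99 |
| 0.5 SD, r = 0 | 0.34 | 0.12 | 0.59 |
| 0.5 SD, r = 0.5 | 0.34 | 0.05 | 0.87 |
| 0.5 SD, r = 0.7 | 0.34 | 0.03 | 0.98 |

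The chance that exactly one side is significant is 2 × (single − both). At the planned effect this is 2 × (0.88 − 0.76) = 0.24. At 0.5 SD it runs from 2 × (0.34 − 0.12) = 0.44 to 2 × (0.34 − 0.03) = 0.62. This is the outcome for which the plan has no reading.

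**Step 5: both ratios rise equally in the active arm.** Imbalance does not change. At the planned effect the left test is still significant in about 88% of trials, the difference test in about 5%.

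**Step 6: only the left side moves.** The standardized effect on the difference is d/√(2(1 − r)), which is below d when r < 0.5. At 0.5 SD its power is 0.19 at r = 0 and 0.26 at r = 0.3, against 0.34 for the left test.

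**The case against.** A reader might infer that no planned test addresses the hypothesis, or that separate tests can never establish a change in imbalance. The documents do not support either. Expected Results also gives the hypothesis as left up with right down during the linguistic tasks, and both ratios are on the list for those tasks. If both are significant in opposite directions relative to sham, left minus right has increased. That is a stricter result than a significant difference score.

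A reader might also infer that the separate tests are badly underpowered. That holds at 0.5 SD, which is a chosen value. At the planned effect each has 0.88 before Bonferroni. Nor is the difference score always better (Step 6), and a significant difference can come from one side alone, which would not meet the two-sided prediction.

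A general arousal shift common to both arms cancels in Phase × Condition. A shift in the active arm only would raise the right ratio, against the prediction, and the right-side test could show that.

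Finally, the article is condensed, and its summary prediction suggests that a test of imbalance is intended. But Data Analyses presents its measures as a full enumeration, names the only two factors and leaves imbalance out. This is a mismatch between two statements in the same document, and not a detail left for an analysis plan.

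What stands is that imbalance has no direct test and no rule says that both sides must be significant.

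**Conclusion.** The concern holds in this form: the stated aim and the predicted interaction concern imbalance, and no listed measure or model tests imbalance directly. The separate tests cover its components, but a result on one side alone does not show a changed imbalance, and the plan does not say that both are required.

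Relying on both being significant costs power when the effects are equal and opposite: about 0.76 against at least 0.99 at the planned effect, and 0.12 to 0.03 against 0.59 to 0.98 at 0.5 SD. These sizes rest on the assumed ρ = 0.5, on r between 0 and 0.7 and on no Bonferroni adjustment. The mismatch itself rests on none of them.

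**What to change.** In Data Analyses, add the TP7–TP8 β/θ difference during each linguistic task, before and after training, as a dependent measure. Testing Phase × Condition × Hemisphere is equivalent. Name it as the test of the imbalance hypothesis. Keep the separate left and right ratio tests, and state that they show whether both sides moved as Expected Results predicts.

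No new data are needed: both channels are recorded before and after training and the index is already defined. If η² = 0.06 and ρ = 0.5 applied to the difference score, its power at 40 participants would be the same 0.876 before Bonferroni, so the sample size need not change on the article's own inputs.

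The cost is a slightly larger Bonferroni family. If the family were only the EEG measures now listed (2 sides × 2 bands × 2 tasks = 8, plus 2 ratios × 3 states = 6, so 14; an assumption), two additions would move the per-test α from 0.05/14 = 0.0036 to 0.05/16 = 0.0031. Power for a single test at the planned effect is 0.54 with 14 tests and 0.49 with 20, so with 16 it lies between these.

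### The 0.87 power for a medium effect rests on an unstated pre-post correlation of 0.5, means a 1-SD difference in change, and ignores the planned Bonferroni correction

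*Protocol article*

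**What the plan says.** The Participants section sets the size: "Forty participants will be enrolled in the study". The Procedure section gives two arms at 1:1, so 20 per arm.

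The Data Analyses section plans, for each dependent measure, "a mixed factorial ANOVA 2 × 2, considering Phase (pre vs. post) and Condition (experimental vs. sham) as the independent variables". It then commits to a Bonferroni correction for multiple comparisons. The next sentence justifies the sample size: "A sample size of 40 was calculated to be enough to achieve a statistical power of 0.87, for medium effect size". That sentence puts the effect at an eta-squared of 0.06 and the significance level at 0.05, and it applies the figure to the planned GLMs.

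The Expected Results section names the effect of interest as the Phase × Condition interaction on the bilateral temporo-parietal imbalance.

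The article gives no pre-post correlation. It does not say whether eta-squared is total or partial, and it does not give the number of tests that share the Bonferroni correction.

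**The concern.** This sentence is the article's only justification of the sample size. It tells the reader that 40 participants give nearly 90% power for an effect of conventional medium size in the planned tests. A reader who takes 0.06 as the partial eta-squared that a mixed ANOVA usually reports for an interaction would expect the trial to find such an effect in almost nine cases out of ten. A non-significant interaction could then be taken as good evidence against a medium effect. If 0.87 in fact belongs to a much larger difference in change, and to an uncorrected alpha, that inference fails.

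**Working it through.** **Inputs.** From the article: N = 40, 1:1 (20 per arm), two phases (m = 2), alpha 0.05, eta-squared 0.06. Hence f² = 0.06/0.94 = 0.0638 and f = 0.253; the conventional medium f is 0.25, with f² = 0.0625. Assumed, because not stated: the pre-post correlation r and the number of Bonferroni tests k.

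**Test.** With two phases and two arms, the Phase × Condition F test has 1 and 38 degrees of freedom and is identical to the two-sample t-test on pre-post change. Power comes from the noncentral F with noncentrality λ.

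**1. Reproducing 0.87.** The standard formula for the within-between interaction is λ = N·m·f²/(1 − r). With r = 0.5:
- f = 0.25: λ = 40 × 2 × 0.0625/0.5 = 10.0, power 0.869.
- eta-squared 0.06: λ = 40 × 2 × 0.0638/0.5 = 10.21, power 0.876.

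Both match the stated 0.87. Other readings that were tried do not: 80 independent observations give 0.61, and the between-arm main effect at r = 0.5 gives 0.44.

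**2. Dependence on r.** Same formula, eta-squared 0.06:

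| r | λ | power |
|---|---|---|
| 0 | 5.11 | 0.60 |
| 0.3 | 7.29 | 0.75 |
| 0.5 | 10.21 | 0.88 |
| 0.7 | 17.02 | 0.98 |

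**3. What the effect is in terms of change.** Let d be the between-arm difference in change, in SDs of the change score. Then λ = N·d²/4 = 10·d².
- Power 0.87 needs λ = 10.03, so d = √(10.03/10) = 1.00.
- The interaction's partial eta-squared is then λ/(λ + N) = 10.03/50.03 = 0.20.
- For comparison, d = 0.5 gives power 0.34 and d = 0.8 gives 0.69.

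The link to the word medium is this: f = 0.25 is scaled to the raw within-cell SD, so the interaction is a difference in differences of 4 × 0.25 = 1.0 raw SD. The SD of change is √(2(1 − r)) raw SDs, which is 1 at r = 0.5, so the two scales coincide there. On the raw-variance scale, eta-squared is 0.0625/1.0625 = 0.059, the stated 0.06.

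**4. If 0.06 is the interaction's own partial eta-squared.** λ = N·f² = 40 × 0.0638 = 2.55, d = √(2.55/10) = 0.505, power 0.344. A simulation of 40,000 t-tests gives 0.345; at d = 1.0 it gives 0.868.

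**5. Bonferroni.** Keep the favourable effect (d = 1.0, λ = 10) and use alpha 0.05/k:

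| assumed k | alpha | power |
|---|---|---|
| 1 | 0.05 | 0.87 |
| 2 | 0.025 | 0.79 |
| 5 | 0.01 | 0.67 |
| 10 | 0.005 | 0.58 |

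**The case against.** **The figure is correct in its own convention.** The article writes eta-squared, not partial eta-squared, and a standard formula gives 0.87 at r = 0.5. This stands. A reader might infer that the authors miscalculated, or that true power is 0.34. The article supports neither: 0.34 answers a different reading of 0.06 and is not a corrected value for the stated one.

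**The correlation could be higher than 0.5.** This also stands. Pre and post measures come from one session, and at r = 0.7 power in the plan's convention is 0.98. The detectable difference in raw SDs is 1.0 × √(2(1 − r)), which is 0.77 at r = 0.7 and 0.63 at r = 0.8. It is therefore wrong to say that the trial can detect only a 1-SD difference on the raw outcome scale. The statement that holds whatever r is concerns 1.0 SD of the change score.

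**A condensed article may leave r and the eta-squared definition to a fuller document.** Their absence alone would not be a finding. But the article does publish a specific power for a labelled effect in the planned tests, and the label does not convey what that power is for. The alpha mismatch lies between adjacent sentences of the article and is not a matter of missing detail.

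**Bonferroni might be meant only for follow-up contrasts.** The text does not say so. It comes directly after the list of dependent measures, and both factors have just two levels, so I take it to cover the separate ANOVAs.

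**The remark on limited effects.** A reader might see a contradiction with Expected Results, which speaks of a limited effect, "due to the potential limited effect size of a novel single-session NF protocol in DD". That phrase explains why the behavioural measures are exploratory. The hypothesised effect is neurophysiological, so this is no contradiction.

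**Conclusion.** The point holds as a misleading statement of power, not as an arithmetic error. Two conclusions are firm:

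- With 20 per arm at unadjusted two-sided 0.05, 0.87 power belongs to a between-arm difference in change of 1.0 SD of the change score (interaction partial eta-squared about 0.20). This needs no assumption about r.
- The stated power is for alpha 0.05, while the same section plans Bonferroni. For any correction over two or more tests, power at that 1-SD effect is 0.79 or lower.

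The rest is conditional. Power is about 0.34 only if 0.06 is the interaction's partial eta-squared. The range 0.60 to 0.98 covers assumed correlations from 0 to 0.7. The Bonferroni figures of 0.79, 0.67 and 0.58 assume 2, 5 and 10 tests, since the article gives no count. A correlation well above 0.5 would offset part or all of the Bonferroni loss for the effect as the plan defines it.

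**What to change.** Keep 40 participants and replace the power sentence, for example with: *40 analysed participants (20 per arm) give 0.87 power at unadjusted two-sided 0.05 for a between-arm difference in pre-post change of 1.0 SD of the change score (interaction partial eta-squared about 0.20), and about 0.34 for a partial eta-squared of 0.06.*

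Alongside it:
- state the assumed pre-post correlation and which eta-squared is meant;
- give the power at the Bonferroni-corrected alpha for the number of tests actually corrected;
- do not call the detectable effect medium without that definition.

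The cost is a sentence or two of text. Sample size, design, analysis and conduct do not change; the stated sensitivity becomes less favourable.
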